### Quality control

2.12

This protocol has been revised based on suggestions of experienced acupuncturists before conducting the trial. All researchers will receive intensive training courses to master the standard operating procedures. Procedures of fNIRS examinations will be trained by specific experts in this field. Case report forms will be verified by monitors at regular intervals throughout the study. In addition, economic compensation will be adopted to improve participant compliance and reduce dropouts.

## Discussion

3

Systematic studies on meridians in China could date back to the 1950s.^[8]^ After a long period of investigations, despite that the physical essence of meridians remains a mystery, a great number of studies reveal various distinctive biological properties of meridian paths as relative to non-meridian regions, such as low electrical resistance,^[17]^ increased temperature,^[18]^ vigorous blood perfusion,^[19]^ low hydraulic resistance^[20]^ along meridians. Apart from these biological properties of meridians, metabolic characteristic is relatively a new research hotspot and needs further investigation. Metabolic characteristic is one of the major properties of meridians and acupoints. The specific metabolic characteristic of tissues underneath the skin surface has certain correlations with meridians. For example, SX Zheng et al^[21]^ found that in physiological condition, the oxygen metabolism along the pericardium meridian was significantly more vigorous than its bilateral non-meridian paths. Given that fNIRS is a recently developed spectroscopic technique to monitor oxygenation metabolism and has advantages of noninvasiveness, ease of use, dynamic detection, and high temporal resolution,^[22]^ it is receiving increasing attention in acupuncture trials.^[23,24]^ Because near-infrared light can penetrate into the tissue deeply to detect change in tissue oxygenation very sensitively,^[25]^ the oxygen-dependent absorption of light by haemoglobin enables the calculation of relative changes of specific parameters reflecting the condition of oxygenation metabolism by fNIRS,^[26]^ such as regional oxygen saturation that assessed in the present study. Oxygen saturation results from a dynamic balance between O_2_ supply and consumption in arteriolar, capillary and venular beds and it is generally regarded that local oxygen saturation has close correlation to regional energy metabolism and blood perfusion.^[27]^

Nevertheless, the majority of previous studies were designed to investigate the correlation between 1 meridian and its corresponding organs, or the difference between meridians (or acupoints) and non-meridians (or non-acupoints). Investigation on the correlation and specificity between 1 meridian and the other meridian is very rare.^[28]^ Thus, there are several highlights and advantages of the present study.

First, as far as we are concerned, the present study is the first case-controlled trial that designed to investigate the correlation and specificity between 2 different meridians (ie, the Heart meridian and the Lung meridian) by using an objective assessment technique, fNIRS. We propose a hypothesis that during the change from the physiological to pathological state, the metabolic characteristics of the affected meridian will change synchronously. And significant difference in the metabolic characteristics might be detected between the affected meridian (ie, the Lung meridian for COPD patients) and the unaffected meridian (ie, the Heart meridian for COPD patients). Meanwhile, in the healthy control group, we put forward a hypothesis that the stimulated meridian will present with more significant change in the metabolic characteristics in relative to the non-stimulated meridian. Given that a previous study revealed that thermal stimulation could significant increase local oxygen saturation,^[24]^ in this study, moxibustion is selected as the stimulation modality. Specifically, on the one hand, the specificity of meridian-visceral association will be explored based on a metabolic comparison in the Heart and Lung meridians between the healthy control group and the CPPD group. On the other hand, the specificity of site-to-site association will be determined based on the comparison of the metabolic change between the 2 meridians that induced by moxibustion in the Heart meridian and Lung meridian, respectively, in the healthy control group.

Second, based on comparison upon the metabolic differences of the Heart and Lung meridians in healthy adults and COPD patients, it will verify whether fNIRS is validated as an add-on technique to assist diagnosis of specific diseases that affects oxygen metabolism in tissue, such as COPD. Previous studies revealed that low oxygen saturation could be detected in peripheral vessels in COPD patients.^[29–31]^ Similarly, based on the theory of meridian-viscera association in traditional Chinese medicine, pathological changes of internal organs will manifest in the external regions or acupoints that belongs to the diseased meridian, and this phenomenon is confirmed by a number of modern studies.^[32,33]^ Nevertheless, it remains unclear whether the distribution regions of the Lung meridians present with abnormal oxygen metabolism in relative to distribution regions of the other meridians or non-meridian paths, which will be verified by the findings of our study.

Third, various kinds of measures will be made to minimize the confounding factors that affect the tissue oxygen metabolism. In details, an experimental room with controlled temperature and humidity is set up and participants are asked to rest for a long period to adapt to the environment. All fNIRS examinations are performed at about the same period of the day. Meanwhile, stimulating food or drink, and exercise are restricted before fNIRS examinations. Fundamental physiological parameters will be measured before and immediately after fNIRS examinations, with the aim to eliminate the possibility that the change of oxygen metabolism is resulted from significant change of fundamental physiological parameters in normal state. Moreover, in order to minimize individual differences, the ratio of participant gender is controlled as 1:1 and the age between the COPD group and the healthy group will try to be matched as much as possible.

Nevertheless, several limitations of the present study should be emphasized. First, due to the exploratory nature as a pilot trial, the study involves a small sample size. Nevertheless, this pilot study will determine whether the feasibility of the study design is validate and provide data for a large scale study in the future. Second, although various measures will be adopted to minimize external and internal factors that affect tissue oxygen metabolism, given that individual differences might be inevitable in some cases, which will reduce the reliability of fNIRS results in a certain extent.

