### Outcomes

2.7

The primary outcome will be regional oxygen saturation of the aforementioned sites that located in the Heart and Lung meridians. Second outcomes will be fundamental physiological parameters measured before and immediately after fNIRS examinations, including body temperature, heart rate, breathing rate, and blood pressure.

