### Data collection and statistical analysis

2.11

SPSS 17.0 for Windows (SPSS Inc., Chicago, IL) will be used to perform statistical analysis. For data expression, numeric data in normal distribution will be presented as mean and standard deviations, and data in skewed distribution will be presented as median and interquartile ranges. For statistical analysis methods, change in continuous variables at different time points will be analyzed by repeated measures analysis of variance. The changes within the groups will analyzed via the paired samples *t*-test, whereas differences between the groups will be compared via the independent samples *t*-test. If data is in skewed distribution, nonparametric test will be applied to perform within-group or between-group comparison. Statistical significance is defined as a *P*-value less than .05.

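### Before/after vital signs, tested only at P<.05 and with no adjustment of rSO2 named, cannot bear the Discussion's aim of eliminating a physiological explanation, least of all for COPD versus healthy control

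*Protocol article*

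**What the plan says.** Section 2.7 makes the vital signs secondary outcomes: "fundamental physiological parameters measured before and immediately after fNIRS examinations, including body temperature, heart rate, breathing rate, and blood pressure". It does not limit them to one group.

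The Discussion, under the third highlight, places them among the measures meant to reduce confounding of tissue oxygen metabolism and gives their purpose: "with the aim to eliminate the possibility that the change of oxygen metabolism is resulted from significant change of fundamental physiological parameters". The sentence then closes with a qualifier about the normal state. The next sentence concerns sex ratio and age matching of the COPD and healthy groups.

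On analysis, section 2.11 says "The changes within the groups will analyzed via the paired samples" *t*-test, and that "differences between the groups will be compared via the independent samples" *t*-test. Repeated measures ANOVA covers several time points, and nonparametric tests cover skewed data. Significance is a *P*-"value less than .05". No margin, confidence interval or adjustment of rSO2 for vital signs is named.

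Under section 2.6.2 the COPD and healthy control groups have one 10-minute recording after 15 minutes of stabilisation, with no intervention. The healthy intervention group is measured before, during and after moxibustion.

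**The concern.** A significance test that finds no change does not show that there was none. With 40 people, changes of moderate size are often missed, so such a result cannot eliminate a physiological explanation.

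For COPD versus healthy control there is a further problem. That comparison is of rSO2 levels between different people at rest. The competing explanation is that the groups differ throughout in heart rate, breathing rate, temperature or blood pressure. Change from before to after a quiet recording does not measure that difference.

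At stake is whether a group difference in rSO2 that reflects general physiology is reported as a property of the Lung meridian, or as support for fNIRS in the diagnosis of COPD. The readings needed to examine this are already collected.

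**Working it through.** **Inputs from the protocol.** Total 120 in a 1:1:1 ratio (section 2.2), so 120/3 = 40 per group. Significance level .05 (section 2.11). The protocol gives no effect size, SD or power, so it has no figure of its own to reproduce.

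**Assumptions.** Two-sided tests; effects in SD units; the correlations stated below.

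**1. Within-session change (moxibustion arm), paired t-test, n=40.** Noncentrality = d × √40, critical t(39) = 2.02, miss rate = 1 − power; d is in SDs of the change.

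| d | Noncentrality | Power | Miss rate |
|---|---|---|---|
| 0.3 | 1.90 | 45.7% | 54% |
| 0.4 | 2.53 | 69.4% | 31% |
| 0.5 | 3.16 | 86.9% | 13% |

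The 95% CI half-width is 2.02/√40 = 0.32 SD. A change of 0.5 SD would usually be seen; one of 0.3 SD is missed more often than not.

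**2. Vital-sign levels, COPD versus control, independent t-test, 40 vs 40.** Noncentrality = d × √(40/2), critical t(78) = 1.99.

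| d | Noncentrality | Power | Miss rate |
|---|---|---|---|
| 0.3 | 1.34 | 26.3% | 74% |
| 0.4 | 1.79 | 42.4% | 58% |
| 0.5 | 2.24 | 59.8% | 40% |

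The 95% CI half-width is 1.99 × √(2/40) = 0.45 SD.

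**3. Effect on an unadjusted single-site rSO2 test.** Suppose one vital sign differs by 0.5 SD between groups, correlates ρ with rSO2, and there is no other group effect. The induced rSO2 difference is ρ × 0.5 SD.

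| ρ | Induced difference | Noncentrality (× √20) | Rejection rate |
|---|---|---|---|
| 0.3 | 0.15 SD | 0.67 | 10% |
| 0.5 | 0.25 SD | 1.12 | 20% |
| 0.7 | 0.35 SD | 1.57 | 34% |

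Simulation with 40,000 replicates gives 0.100, 0.197 and 0.340. Adjusting for that vital sign gives 0.051, 0.050 and 0.052. The return to 5% is built in, because the simulated effect acts only through the adjusted variable.

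**4. The same-person comparator.** A second simulation (20,000 runs, 40 per group, correlation 0.7 between sites) shifts a systemic component common to both sites by 0.5, 0.8 or 1.0 SD. The Lung-site COPD-control test is significant in 46%, 84% and 96% of runs. The between-group test of the Lung-minus-Heart difference is significant in 4.8%, 5.3% and 5.2%. A shift common to both sites cancels in that contrast.

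**5. Would an equivalence test serve instead?** For a paired test with two one-sided 5% tests, 80% power and true change 0, n = ((1.645 + 1.282)/margin)². This gives 215, 96, 54 and 35 for margins of 0.2, 0.3, 0.4 and 0.5 SD. Forty people suffice only for a margin of nearly 0.5 SD, so intervals are the more practical report.

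**The case against.** A reader might infer that the protocol will declare a physiological explanation excluded whenever the vital-sign tests are non-significant. The text does not go that far. It states an aim, gives no decision rule, and does not say whether a significant change means P<.05. That reading is an inference from the Discussion sentence taken together with section 2.11.

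A reader might also infer that the protocol applies the wrong test to the COPD-control comparison. The sentence speaks of a change in oxygen metabolism in the normal state, which fits the moxibustion arm at least as well, and there the before/after reading is the relevant quantity. The wording is not conclusive, because the Discussion also describes the move from health to disease as a change in metabolic characteristics, and section 2.7 collects vital signs without restriction by group. Section 2.11 also permits an independent t-test on vital-sign levels, so a comparison of levels is available; its weakness is low power, shown above.

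The design has an internal comparator in the Heart meridian, which protects the specificity question against a shift common to both sites. This objection stands, with one reservation: section 2.11 does not name the between-group comparison of the Lung-minus-Heart difference. Nor does that contrast settle whether an rSO2 level helps to diagnose COPD.

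The pass rate of a before/after test when nothing changes during the recording merely restates the significance level and does not measure harm. Adjustment is itself debatable, since altered heart or breathing rate may be part of COPD. Finally, the Discussion calls the study an exploratory pilot and concedes that individual differences may remain, though it does not withdraw the stated aim.

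**Conclusion.** The point holds in limited form. The stated aim is stronger than the named analyses can deliver. For moxibustion the right quantity is measured, but a non-significant paired test at n=40 leaves a 0.3-SD change undetected 54% of the time. For COPD versus healthy control, before/after change does not bear on standing differences, and a test of levels misses 0.5 SD 40% of the time.

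The possible inflation of a single-site rSO2 comparison, 10% to 34% against 5%, rests on an assumed 0.5-SD vital-sign difference, assumed correlations of 0.3 to 0.7 and no other group effect. It does not apply to a Lung-minus-Heart contrast if the effect is common to both sites. The documents do not support saying that the protocol treats non-significance as proof. This is an inexpensive improvement in analysis and wording, not a flaw that invalidates the design.

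**What to change.** In section 2.11:

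- Report COPD-control differences in the pre-examination temperature, heart rate, breathing rate and blood pressure with 95% CIs.
- Beside the unadjusted COPD-control rSO2 contrast, add as a sensitivity analysis the same contrast from a linear model adjusted for those pre-examination values.
- Base the meridian-specificity conclusion on the between-group comparison of the within-person Lung-minus-Heart difference.

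In the Discussion, say that the vital signs are used to assess, not eliminate, a physiological explanation, and that a non-significant vital-sign test is not taken as evidence of no systemic explanation.

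The cost is wording and one extra model, with no new data, visits or participants. The model uses four degrees of freedom, or five if systolic and diastolic pressure enter separately, out of 40 + 40 − 2 = 78. The adjusted contrast may remove part of the COPD effect itself, which is why the unadjusted contrast stays beside it.

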## Conclusions

4

By comparing the metabolic characteristics of the Heart and Lung meridians via fNIRS, the present case-controlled trial aims to investigate the association and specificity of different meridians. Besides, it will verify whether fNIRS is validated as an add-on technique to assist diagnosis of COPD. The findings of this study are expected to bring scientific evidence for traditional meridian theory and promote the selection of acupoints in clinical practice.
